### Secondary study parameters

The Kaplan-Meier method will be used to estimate PFS and OS proportions per treatment group at appropriate time points, while the Greenwood estimate of the SE (standard error) will be used to construct the corresponding 95% CI. Multivariate cox proportional hazards models will be built for PFS and OS where treatment group effect will be corrected for minimisation factors age group (≤55 years vs >55 years), KPS (80–90 vs >90) and left or right hemisphere. Additionally, competing risk analysis will be used to calculate cumulative incidence of PFS (with competing risks progression/relapse and death without progression/relapse which add up to 100% at every time point). Oncofunctional outcome will be evaluated using a scatter or bubble plot with volumetric data on the x-axis and neurological status (NIHSS) or patient performance (KPS) on the y-axis. SAEs in both groups will be described.

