## Methods and analysis

### Study design

This is a international, multicenter, prospective, three-arm cohort study. Eligible patients are operated using awake mapping, asleep mapping or no mapping with a 1:1:1 ratio with a sequential computer-generated random number as subject ID. Patients with motor-eloquent tumours will be treated in all study arms, while speech-eloquent tumours will only be treated in either the awake mapping or no mapping arm. The PROGRAM study (prospective cohort study of high-grade glioma resections using awake craniotomy and intraoperative stimulation mapping) is similar to the SAFE-trial (SAFE surgery for glioblastoma patients: awake craniotomy versus craniotomy under general anesthesia: a multicenter randomized controlled trial) and is initiated by the same center, however, the presented study will be different in various ways: the PROGRAM study (1) will be an observational, prospective cohort study, (2) will include asleep mapping as an additional treatment arm, (3) will evaluate the extent of resection of the non-contrast-enhancing part of the tumour as well, (4) will include both WHO grade III and grade IV gliomas, (5) will include an oncofunctional score as one of the outcomes and (6) will include neurosurgical centers in the USA and is part of the ENCRAM Research Consortium.^18^

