
Bern protocol: the following details are different to the above-mentioned protocol. Total intravenous anesthesia without inhalation agents is used (TIVA-only). A bolus of propofol is started (1–2mg/kg body weight) with fentanyl (1–2 mg/kg body weight), and remifentanil (1–2 mg/kg body weight) and maintained with propofol (100–200 mg/kg/min) and remifentanil (0.5 mg/kg/h). A short-acting relaxant is used (Esmeron 0.6 mg/kg body weight for the purpose of intubation. Then, the ‘train-of-four’ technique is used involving percutaneous stimulation of the right median nerve (40 mA, 0.2- msec pulse duration) to test recovery from muscle relaxation. MEPs are recorded from subdermal electrodes in order to quantify the evoked responses. A combination of DCS MEP via a four-contact strip electrode placed on the pre-central gyrus for focal and selective stimulation and a back-up TES MEP via scalp electrodes is used.^20^ The ‘suction probe’ (INOMED medizintechnik, Germany; #525 650) is used for cortical mapping and subcortical continuous dynamic mapping.^21^ For subcortical stimulation a monopolar cathodal pulse stimulation is used with train of 5 pulses of 0.5 msec duration, ISI 4 msec and 2 Hz repetition rate. The mapping intensities range from 20 mA down to 3 mA (and in selective cases down to 1mA). Monitoring motor function is continued until dura closure in order to detect vascular injuries (for instance due to vasospasms).

(3) Craniotomy under GA without mapping (arm 3: no mapping).

On the evening before surgery, 1.5–2.0 mg lorazepam is administered for anxiolysis.Sixtey min before anaesthesia induction, the patient receives 1 g paracetamol orally and 7.5–15 mg midazolam orally if requested for sedation. En route to the operating room, 0.5–2 mg midazolam intravenous may be given. 1 g cefazoline is given intravenous for antibiotic prophylaxis before anaesthesia induction. GA is induced intravenously with fentanyl 0.25–0.5 mg, propofol 100–200 mg and cis-atracurium 10–20 mg. After induction of anaesthesia, the patient is orotracheally intubated and mechanical ventilation is applied. Respiratory rate and tidal volume are adjusted to keep the patient normocapnic.

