### Study procedures: clinical evaluations and follow-up

Preoperative (baseline) CRF (Case Report Form).Unique subject ID, demographics (centre, year, gender, age), tumour-specific factors (tumour volume preoperative, tumour hemisphere and lobe; eloquent areas), patient specific factors: preoperative KPS, ASA score, neurological status (NIHSS), MRC grade arm/leg (for motor-eloquent tumors), neurolinguistic testing, MOCA, QoL questionnaires (QLQ-C30, QLQ-BN20, EQ-5D).Surgery CRFType of ISM, surgeon’s rationale for modality, surgeon’s goal, use of preoperative steroids (if yes: clinical improvement, conversion to mapping possible); use of surgical adjuncts (if DTI: integrity of tracts), use of additional imaging, radiological factors: resection percentage (both the contrast-enhancing and non-contrast-enhancing part), residual volume and postoperative ischaemia.Follow-up CRFsSix weeks postoperatively: histology and molecular markers (WHO grade, MGMT status, IDH-1 status), neurological status (NIHSS), MRC grade arm/leg, status MRC arm/MRC leg/facialis/speech/visual (new, worsened, improved, stable), KPS, QoL questionnaires (QLQ-C30, QLQ-BN20, EQ-5D).Three months postoperatively: neurological status (NIHSS), MRC grade arm/leg, status MRC arm/MRC leg/facialis/speech/visual (new, worsened, improved, stable), KPS, neurolinguistic testing, MOCA, QoL questionnaires (QLQ-C30, QLQ-BN20, EQ-5D).Six months postoperatively: neurological status (NIHSS), adjuvant treatment, MRC grade arm/leg, status MRC arm/MRC leg/facialis/speech/visual (new, worsened, improved, stable), KPS, MOCA, QoL questionnaires (QLQ-C30, QLQ-BN20, EQ-5D).Twelve months postoperatively: PFS, OS (end of study).

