### Data collection

All patient data are collected using the electronic data software Castor EDC (Electronic Data Capture). This software allows built-in logical checks and validations to promote data quality. Data entry and group allocation is performed by the study coordinator or locally by trained physicians and research nurses under supervision of the local investigator.

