### Primary study parameters

The primary endpoints will be analysed using multivariate logistic regression. Subgroup analyses for tumour grade (WHO grade III/IV), preoperative neurological morbidity, preoperative tumour volume, patient’s age (in 10-year age brackets) and tumour location/eloquence will be performed.

We will be including a stratification factor in the primary analysis model with each 10 observed events using the order of prognostic value as mentioned in the paragraph above, where the first 10 events will be used to estimate the effect of the arm. This rule will be applied in case less than 40 patients in total develop neurological deterioration. In the so constructed multivariate logistic regression model the treatment arm effect will be tested at 4% significance level. The primary analysis of proportion of patients without residual contrast-enhancing and non-contrast-enhancing tumour consist of a multivariate logistic regression, where arm effect is corrected for all minimisation factors. In this model the group effect will be tested at 1% significance level. Manual or semiautomatic segmentation will be performed on axial T1 and T2/FLAIR MRI contrast enhanced slices to measure preoperative and postoperative tumour volume. A determination of volumes will be calculated blinded for the treatment group.

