### Study monitoring

No scheduled on-site monitoring visits will be performed. Local investigators will remain responsible for the fact that the rights and well-being of patients are protected, the reported trial data are accurate, complete and verifiable from source documents and the conduct of the trial is in compliance with the currently approved protocol/amendment(s), with GCP (Good Clinical Practice) and with the applicable regulatory requirement(s). Direct access to source documentation (medical records) must be allowed for the purpose of verifying that the data recorded in the CRF are consistent with the original source data. No data safety monitoring board will be installed: all interventions are care-as-usual and patients are allocated without randomisation.

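### Centre is recorded but appears in none of the stated models, so in this non-randomised multicentre cohort arm effects may be confounded with centre, and standard errors will be too small to the extent that technique clusters by centre

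*Protocol article*

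**What the plan says.** Centre is collected. The baseline case report form in Study procedures lists "Unique subject ID, demographics (centre, year, gender, age" and further items.

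The model covariates are set out under Data analysis:

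- **Endpoint 1 (NIHSS deterioration), Primary study parameters.** Logistic regression. If fewer than 40 patients deteriorate, the first 10 events serve the arm effect, and one factor enters for each further 10. The order is that of the preceding paragraph: tumour grade, preoperative neurological morbidity, preoperative tumour volume, age, location/eloquence. Test at 4%.
- **Endpoint 2 (no residual tumour), Primary study parameters.** Logistic regression in which "arm effect is corrected for all minimisation factors". The factors are not named there. Test at 1%.
- **PFS and OS, Secondary study parameters.** Cox models "corrected for minimisation factors age group (≤55 years vs >55 years), KPS (80–90 vs >90) and left or right hemisphere". This is the only place where the minimisation factors are named.

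No centre term, random effect, stratification by centre or cluster-robust variance is mentioned.

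On how patients reach an arm, Study monitoring says that "all interventions are care-as-usual and patients are allocated without randomisation". Data collection says that "Data entry and group allocation is performed by the study coordinator or locally by trained physicians and research nurses". Study design describes treatment "with a 1:1:1 ratio with a sequential computer-generated random number as subject ID"; the random number is the subject identifier, and the ratio is not said to hold within centres. The surgery form records the surgeon's reason for choosing the modality. Interventions describes asleep mapping through the procedures of two named centres, the second introduced by "Bern protocol: the following details are different to the above-mentioned protocol".

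**The concern.** Without randomisation, any variable linked to both technique and outcome can bias the arm comparison, and centre is an obvious candidate.

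- **Link to technique.** The Introduction says that there is no international consensus on using these techniques, so usual care may well differ between sites. Allocation may be done locally.
- **Link to outcome.** Imaging and fluorescence adjuncts are left to the surgeon (Surgical adjuncts). Segmentation may be manual or semiautomatic, with differing software (Primary outcome measures). There are no scheduled on-site monitoring visits. Volumes are determined blinded to group, but no blinding of the NIHSS rating is stated.

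Two different things are at stake. One is bias: a difference between hospitals could be reported as a difference between techniques. The other is precision: if patients of one centre share outcome risk and also tend to share an arm, a model that treats them as independent understates the standard error, and the 4% and 1% tests reject too often.

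**Working it through.** The point disputes no figure in the plan, so there is none to reproduce. The check asks what the listed covariates can absorb and how large the error could be.

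**1. Room in the endpoint 1 model.** Inputs from Sample size: 137 patients per arm, deterioration 10% without mapping and 3% in each mapping arm.

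- Expected events: 137 × 0.10 + 274 × 0.03 = 13.7 + 8.2 = 21.9, about 22.
- Pooled rate: 21.9 / 411 = 5.3%.
- Since 22 < 40 the entry rule applies: 10 events for the arm, 10 for one factor. The model holds arm and tumour grade only. Nothing in it can stand in for centre, and a set of centre indicators could not be fitted.

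**2. Rejection rate when centre is ignored.** The documents give no number of centres, intraclass correlation (ICC) or arm mix, so all of these are assumed: no arm effect; 12 centres of 34 (408 patients, close to 411); a normal centre effect on the log-odds with SD 0.3 / 0.5 / 0.7; each centre uses one preferred technique in a given share of its patients; pooled two-sided z-test of mapping versus no mapping, without covariates.

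| Share on preferred technique | 4% test, base rate 10% | 1% test, base rate 25% |
|---|---|---|
| 33% (balanced) | 4.1 / 4.1 / 4.3% | 1.0 / 0.9 / 1.0% |
| 50% | 3.9 / 4.6 / 4.9% | 1.0 / 1.5 / 2.0% |
| 60% | 4.0 / 5.0 / 7.2% | 1.4 / 2.0 / 3.1% |
| 80% | 5.6 / 8.4 / 11.8% | 2.3 / 4.9 / 9.3% |

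A separate set of runs of the 80% row (6,000 cohorts per setting) gave 5.0 / 7.9 / 11.9% and 2.3 / 5.0 / 8.4%, so the runs agree to within one percentage point. With the pooled rate of 5.3% from step 1 in place of 10%, the 4% test in the 80% row rejects 4.5 / 6.2 / 8.6%.

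**3. Other assumed settings.** Two arms of about 136, 8 or 16 centres, 4,000 runs; SD 0.3 to 0.5 for endpoint 1 and 0.3 to 0.8 for endpoint 2:

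| Arm mix | Endpoint 1, nominal 4% | Endpoint 2, nominal 1% |
|---|---|---|
| Balanced within centre | 3.3 to 3.7% | 0.65 to 1.05% |
| 80/20 | 4.1 to 6.2% | 1.1 to 8.2% |
| One technique per centre | 5.0 to 12.6% | 2.5 to 22% |

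**4. Extreme case by formula.** If each centre used one technique only, the design effect is DE = 1 + (m − 1) × ICC, the model standard error is 1/√DE of the true one, and the real error rate is 2 × [1 − Φ(z/√DE)], with z the two-sided critical value.

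- m = 10, ICC = 0.01: DE = 1 + 9 × 0.01 = 1.09; standard error ratio 0.96; 4% becomes 4.9%, 1% becomes 1.4%.
- m = 40, ICC = 0.05: DE = 1 + 39 × 0.05 = 2.95; standard error ratio 0.58; 4% becomes 23%, 1% becomes 13%.

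The amount of clustering of technique by centre decides whether there is an error-rate problem at all; the between-centre SD then sets its size.

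**The case against.** The strongest objection is that no passage says that technique follows centre. A reader might infer it from the two centre-specific descriptions of asleep mapping, but these describe how the procedure is done at two sites. They do not say that those sites do only asleep mapping, or that other sites do none. The recorded rationale for the modality points to a surgeon's choice for each patient. Tumour location also drives the arm, since speech-eloquent tumours go only to awake mapping or no mapping. The 1:1:1 ratio might even hold within centres. This objection stands: clustering of technique by centre is plausible but not documented, and the balanced rows above show no material inflation.

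Second, for endpoint 2 the article names no covariates where it describes the model. The absence of centre there rests on reading the list given for the Cox models back into it. That stands as a caveat, although it is the only definition supplied.

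Third, an article may leave clustering to a fuller document, and this one concedes under Strengths and limitations that an observational design does not exclude all bias. This carries less weight. The article does not leave covariates open: it fixes an ordered list, an entry rule and a named set of factors. Followed as written, these leave centre out, and a general caveat about bias does not adjust for it.

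**Conclusion.** The omission is real and should be corrected. Arm effects in the primary and Cox analyses are open to confounding by centre, and standard errors will be too small to the extent that technique clusters by centre.

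The size cannot be derived from the documents. Under the 12-centre assumptions, the nominal 4% test rejects about 4% with arms balanced within centres and about 5% to 12% with an 80% preferred technique (about 4.5% to 8.6% at the 5.3% event rate that the plan's own figures imply). The nominal 1% test rejects about 1% and about 2% to 9%.

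A flat statement that centre determines the arm, or that the standard errors are too small, goes beyond the documents: both need a within-centre arm mix that is not given. Confidence is high that centre is missing from the stated lists and moderate that it matters materially.

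**What to change.** - **Primary models.** Add a centre random intercept to both logistic regressions. Exempt it from the one-factor-per-10-events rule, because about 22 events cannot support centre indicators.
- **Cox models.** Use centre as a stratum or shared frailty.
- **Confounding.** A random intercept deals mainly with correlated errors. It assumes that the centre effect is independent of technique, so it does not remove between-centre confounding. Add a within-centre estimate: for example, include each centre's arm proportions as a covariate, or use conditional or stratified logistic regression.
- **Reporting.** Give an arm-by-centre table, and cluster-robust standard errors as a sensitivity analysis. State that where a centre uses one technique only, the effects of centre and technique cannot be separated.
- **Endpoint 2.** Name its covariates where the model is described.

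The cost is analysis text and some reporting; centre is already on the baseline form. The price is wider intervals. If technique proves largely nested in centre, little within-centre information will remain, and with so few endpoint 1 events the centre variance will be poorly estimated. The report would then have to say so.

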**Methods and analysis:**

This study is an international, multicenter, prospective three-arm cohort study of observational nature. Consecutive HGG patients will be operated with awake mapping, asleep mapping or no mapping with a 1:1:1 ratio. Primary endpoints are: (1) proportion of patients with National Institute of Health Stroke Scale deterioration at 6 weeks, 3 months and 6 months after surgery and (2) residual tumour volume of the contrast-enhancing and non-contrast-enhancing part as assessed by a neuroradiologist on postoperative contrast MRI scans. Secondary endpoints are: (1) overall survival and (2) progression-free survival at 12 months after surgery; (3) oncofunctional outcome and (4) frequency and severity of serious adverse events in each arm. Total duration of the study is 5 years. Patient inclusion is 4 years, follow-up is 1 year.

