### Inclusion criteria

In order to be eligible to participate in this study, a subject must meet all of the following criteria:

Age ≥18 years and ≤90 years.Tumour diagnosed as HGG (WHO grade III/IV) on MRI as assessed by the neurosurgeon.Tumours situated in or near eloquent areas; motor cortex, sensory cortex, subcortical pyramidal tract, speech areas or visual areas as indicated on MRI (Sawaya grading II and II).^19^The tumour is suitable for resection (according to neurosurgeon).Written informed consent.

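### The OS and PFS Cox models adjust for age only as ≤55 versus >55 years, so in this non-randomised cohort part of any confounding by age can remain in the arm comparison

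*Protocol article*

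**What the plan says.** The section Secondary study parameters fixes the survival models: "Multivariate cox proportional hazards models will be built for PFS and OS", with the treatment effect "corrected for minimisation factors age group (≤55 years vs >55 years"), together with "KPS (80–90 vs >90) and left or right hemisphere". Age therefore enters with two values.

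Three other places bear on this:

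- Inclusion criteria: "Age ≥18 years and ≤90 years".
- Study monitoring: "patients are allocated without randomisation". The abstract likewise calls the study a "prospective three-arm cohort study of observational nature".
- Study procedures: age is on the baseline case report form, so the value in years will be available.

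Primary study parameters touches age in two ways. The subgroup list has "age (in 10-year age brackets"). The residual-tumour model is one "where arm effect is corrected for all minimisation factors", but that section does not list the factors. The only list is the one given for OS and PFS.

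**The concern.** A two-class age factor is reasonable when its job is to balance a randomisation. Randomisation then deals with age inside each class, and the model term only reflects the design. This study has no randomisation and so nothing that balances age. The technique is part of usual care, and the case report form asks for the surgeon's reason for choosing it. The age term must therefore remove confounding, and it treats a patient of 56 and a patient of 90 as the same.

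If prognosis worsens steadily with age and mapped patients are younger on average, some of the age difference remains inside the two classes. It would then be read as an effect of mapping on OS and PFS.

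**Working it through.** The protocol states no figure for residual confounding, so there is none to reproduce. The check asks how much of an age effect a cut at 55 leaves behind.

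**Inputs from the protocol:** cut at 55; ages 18–90; no randomisation; 137 evaluable patients per arm.

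**Assumed inputs:** the age distribution, the age effect, the age gap between arms, and 40% dead at 12 months.

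**Step 1, share removed by the cut.** For normal ages, a linear age effect and a pure shift in mean age between arms, the share removed is φ(z)²/[p(1−p)], with z = (cut − mean)/SD and p = Φ(z). For mean 60 and SD 12:

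- z = (55 − 60)/12 = −0.417, φ(z) = 0.366, p = 0.338
- share removed = 0.366²/(0.338 × 0.662) = 0.598, so about 40% remains.

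**Step 2, sensitivity to the age distribution.** The share left is taken as the age variance remaining within the two classes, with ages truncated to 18–90.

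| Assumed ages | Share left, ≤55 vs >55 |
|---|---|
| Mean 60, SD 12 | 39% |
| Means 50–62, SD 10–16 | 34–46% |
| Mean 65, SD 10 | 55% |
| Uniform 18–90 | 25% |

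**Step 3, sensitivity to the shape of the effect.** Cox simulations with 60,000 patients, gaps of 5 or 8 years and a hazard ratio of 1.3 or 1.5 per decade left 0.27–0.59 of the crude log-hazard-ratio bias when the age effect was linear. A pure step at 55 left 0.13, which is within simulation noise of zero. An effect only above age 60 left 0.52.

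**Step 4, translation to a hazard ratio.** Bias in the log hazard ratio ≈ share left × age gap × log hazard ratio per year. With a share of 0.402, a 5-year gap (mapped patients younger) and no true arm effect:

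- 1.02 per year: 0.402 × 5 × 0.0198 = 0.040, hazard ratio 0.96
- 1.04 per year: 0.402 × 5 × 0.0392 = 0.079, hazard ratio 0.92

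A simulated Cox model with 137 v 137 patients gave the same 0.96 to 0.92. In the large simulation (mean 60, SD 12, 5-year gap, 1.5 per decade) the hazard ratio was 0.84 without age, 0.94 with two classes and 1.01 with age in years. An assumed 8-year gap gave 0.94 to 0.87 in the 137 v 137 model.

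**Step 5, effect on the test.** Events ≈ 274 × 0.40 ≈ 110, so the standard error of the log hazard ratio is about 2/√110 = 0.19. The 5-year bias is then 0.040/0.19 to 0.079/0.19, or about 0.2 to 0.4 standard errors. Simulated type I error at a nominal 5% was 5–7% for the 5-year gap and 6.5–9.5% for the 8-year gap. With linear age it was about 4–5%. With 800 runs the Monte Carlo standard error at 5% is √(0.05 × 0.95/800) = 0.8 points, so the low end of the 5-year range cannot be told from nominal.

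**The case against.** **The size is not in the protocol.** A reader might infer that a fixed 40% of age confounding remains. The documents do not support that. The figure needs a near-normal age distribution, a graded effect and an age gap, and none of these is given. The eligibility range alone does not yield it, since uniform ages over 18–90 leave 25%. This objection stands, so only a conditional range can be stated.

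**The consequence is modest.** OS and PFS are secondary endpoints, the 5-year bias is under half a standard error, and the simulations leave out KPS, which is in the model and may absorb some of the age effect. This stands too. It lowers the weight of the point but gives no reason to prefer two classes.

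**Reach to the resection endpoint.** A reader might infer that the residual-tumour comparison is biased in the same way. That section does not list its factors, so the 55-year cut gets there only by reading across to the OS and PFS list. Nor does the protocol say that age predicts complete resection. The point extends to that model only conditionally.

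**Reach to the NIHSS endpoint.** A reader might see the 10-year brackets as a conflicting age coding that also needs changing. They are given for subgroup analyses, and a different grouping there is not a contradiction. They could enter the NIHSS model only through the events rule, where age comes fourth. The sample-size rates imply about 137 × (0.10 + 0.03 + 0.03) ≈ 22 events. At ten events for the arm and ten per added factor, that allows the arm and one factor, so age would not be in the model.

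**Conclusion.** The point holds for the OS and PFS models. The protocol uses a coarse balancing factor as the only age adjustment in a non-randomised cohort, although age in years is collected.

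The harm requires both a graded age effect and an age difference between arms. Given both, about 35–45% of the age confounding remains for near-normal ages around mean 60 and SD 12. The share is about 25–60% over the wider scenarios and near 0 for a pure step at 55. With similar ages in the arms there is little to remove.

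The bias in the hazard ratio is the main argument, at about 0.92–0.96 under an assumed 5-year gap with no true effect. A reader might infer that the survival tests are seriously anti-conservative, but inflation is slight at that gap and reaches 9.5% only under an assumed 8-year gap. Severity is minor to moderate.

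**What to change.** In Secondary study parameters, replace the two-class age term in the OS and PFS Cox models with age in years, either linear or as a 3-knot spline fixed in advance. Keep the 55-year cut for descriptive tables.

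In Primary study parameters, say which factors the residual-tumour model uses. If they are the OS and PFS list, enter age there in the same way. No change to the NIHSS model is needed on this ground.

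The cost is about a sentence of wording per section and no new data. Linear age uses the same single parameter as the present split, and a 3-knot restricted cubic spline uses one more.

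### The endpoint 2, PFS and OS models adjust for minimisation factors that a non-randomised cohort does not have; the only such list leaves KPS below 80 uncategorised and omits preoperative volume, eloquence and, for survival, WHO grade

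*Protocol article*

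**What the plan says.** All references are to the protocol article.

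- **Primary study parameters.** Endpoint 2 is analysed by "multivariate logistic regression, where arm effect is corrected for all minimisation factors", with the group effect tested at 1%. The factors are not listed there.
- **Secondary study parameters.** The Cox models for PFS and OS correct the treatment effect for "minimisation factors age group (≤55 years vs >55 years), KPS (80–90 vs >90) and left or right hemisphere". No other list in the article carries that name.
- **Study design.** The study "will be an observational, prospective cohort study". Speech-eloquent tumours may be treated in the awake mapping or no mapping arm only.
- **Study monitoring.** The reason given for having no safety board is that "all interventions are care-as-usual and patients are allocated without randomisation".
- **Inclusion and exclusion criteria.** Neither list mentions KPS.
- **Study procedures.** The baseline CRF records KPS and "tumour volume preoperative, tumour hemisphere and lobe; eloquent areas". The surgery CRF records the surgeon's rationale for the modality. The six-week CRF records WHO grade, MGMT and IDH-1.

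**The concern.** Minimisation factors are the variables that an allocation algorithm balances. In a randomised trial it is sound to adjust for them, because the design already handles the remaining confounding. Here the surgeon's reasons enter the choice of arm and no algorithm balances anything, so the comparison is only as good as its covariate set.

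The stated set was not built for that task. Preoperative volume and location/eloquence plausibly bear on both the choice of mapping and the chance of complete resection, and they are missing. WHO grades III and IV are pooled in the survival models without adjustment for grade. A patient with KPS below 80 is eligible but fits neither KPS category, so must be dropped or miscoded. That conflicts with the stated intention-to-treat analysis of eligible patients. At stake are the validity of the 1% test on a primary endpoint and the adjusted survival comparisons.

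**Working it through.** **Step 1: does a minimisation exist?** Study monitoring denies randomisation. The random number under Study design serves as a subject ID. The 1:1:1 ratio there and the group allocation under Data collection describe no algorithm. The two analysis sections therefore rely on factors that the design does not supply.

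**Step 2: does the KPS coding cover the eligible population?** The categories are 80–90 and above 90, and eligibility has no KPS limit. KPS below 80 is uncovered. The documents do not say how common it is. If it were 10–20% (assumption), 0.10 × 411 ≈ 41 to 0.20 × 411 ≈ 82 of the 411 evaluable patients would have no category.

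**Step 3: which recorded variables are left out?**

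| Variable | Recorded | Endpoint 2 model | PFS/OS models |
|---|---|---|---|
| Preoperative volume | baseline | not on the list | not on the list |
| Location/eloquence | baseline | not on the list | not on the list |
| WHO grade | 6 weeks | not argued here | not on the list |
| IDH-1, MGMT | 6 weeks | not argued here | not on the list (prognostic) |

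The endpoint 2 column applies the Secondary study parameters list by inference. Eloquence needs no assumption about surgeons' habits: Study design bars speech-eloquent tumours from one arm.

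**Step 4: the basis for an illustration.** The plan gives no figure for the adjusted model. Its sample size for endpoint 2 shows the comparison intended: 25% vs 50%, 1% level, 80% power, continuity correction. With a mean proportion of 0.375,

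n = [2.576·√(2·0.375·0.625) + 0.842·√(0.25·0.75 + 0.5·0.5)]² / 0.25² ≈ 86.1,

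and the continuity correction gives (86.1/4)·[1 + √(1 + 4/(86.1·0.25))]² ≈ 94 per arm, as stated. This is an unadjusted, arm-against-arm calculation. At 411 patients each arm has 137.

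**Step 5: effect of one omitted confounder.** Assumptions, none from the documents: complete resection is 50% in small and 20% in large tumours; mapping has no effect; a share s of mapped patients and 1 − s of unmapped patients have small tumours; volume is not in the model. Then

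- p(mapped) = 0.5s + 0.2(1 − s), and p(unmapped) = 0.5(1 − s) + 0.2s;
- rejection probability = Φ[(d − 2.576·SE₀)/SE₁], where d is the difference, SE₀ = √(2·0.35·0.65/137) = 0.0576 and SE₁ is the unpooled standard error.

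For s = 0.65: d = 0.395 − 0.305 = 0.090, SE₁ = 0.0574, and (0.090 − 0.1484)/0.0574 = −1.02, which gives 0.154.

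| Share small, mapped/unmapped | Apparent rates | Difference | Rejection at nominal 1% |
|---|---|---|---|
| 55/45 | 36.5% vs 33.5% | 3 points | 2% |
| 60/40 | 38% vs 32% | 6 points | 6% |
| 65/35 | 39.5% vs 30.5% | 9 points | 15% |
| 70/30 | 41% vs 29% | 12 points | 31% |

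**The case against.** The strongest reply is that the planners did not overlook these variables. Primary study parameters prespecifies subgroup analyses by grade, preoperative neurological morbidity, preoperative volume, age and location/eloquence, and the same ordered list apparently feeds the endpoint 1 model. The strengths and limitations box also concedes that bias will remain. Both are true, but subgroup analyses do not adjust the endpoint 2 or Cox models, and conceding residual bias does not justify leaving measured confounders out. Nor is this merely detail left to an SAP: the article names the adjustment set, so an SAP that adjusted properly would have to contradict it.

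Some stronger readings are not supported:

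- **That endpoint 2 certainly loses its poorest patients.** The KPS gap is explicit only for PFS and OS. For endpoint 2 the certain defect is a covariate set that is not defined where it is used.
- **That IDH-1 and MGMT confound resection.** They are recorded from tissue at six weeks and cannot directly drive the surgeon's choice. They count as prognostic factors for survival only.
- **That the bias favours mapping.** The documents give no direction. The opposite imbalance would hide a benefit.
- **That the false-positive rate is higher still.** Pooling both mapping arms (274 vs 137) would raise the 65/35 figure to 21%, but the sample size section works per arm.
- **That cutting age at 55 is an error.** It is coarse, but a legitimate choice.

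**Conclusion.** Wrong as written. Two points are certain from the text: the analysis sections rely on minimisation factors in a cohort allocated without randomisation, and the only list so named gives eligible patients with KPS below 80 no category. That list also omits preoperative volume and location/eloquence, and for PFS and OS WHO grade, all of which are recorded. Its use for endpoint 2 is an inference, though the only one the article offers; without it the model for a primary endpoint has no defined covariates.

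The size cannot be computed from the documents. Under the assumed resection rates, omitting volume alone turns a 1% test into one that rejects 2% to 31% of the time when imbalance runs from 55/45 to 70/30. This shows possible bias, not expected bias. The proportion with KPS below 80 is likewise unknown.

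**What to change.** Delete the term minimisation factors from Primary and Secondary study parameters, and prespecify the covariates of each model before outcomes are examined:

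- **Endpoint 2:** preoperative volume (contrast-enhancing, and non-contrast-enhancing where that residual is analysed), location/eloquence, age, KPS over its full range, hemisphere.
- **PFS and OS:** the same, plus WHO grade, with IDH-1 and MGMT as prognostic covariates.
- **All models:** keep patients with KPS below 80.

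The faulty sentences are in the protocol article, so the protocol text needs correcting and any SAP must agree with it. Tumour volume, location, KPS and the markers are already on the CRF, so no new type of data is needed. The cost is a few more parameters per model and a stated way of handling missing IDH-1 and MGMT values.
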